# Implementation of observational pain management protocol to improve pain management for long-term institutionalized older care residents with dementia: study protocol for a cluster-randomized controlled trial

**DOI:** 10.1186/1745-6215-15-78

**Published:** 2014-03-13

**Keywords:** Pain management, Pain measurement, Dementia care, Nursing homes

## Abstract

**Background:**

Systematic use of observational pain tools has been advocated as a means to improve pain management for care home residents with dementia. Pain experts suggest that any observational tool should be used as part of a comprehensive pain management protocol, which should include score interpretation and verification with appropriately suggested treatments. The Observational Pain Management Protocol (Protocol) was therefore developed. This study aims to investigate the extent to which the implementation of this Protocol can improve pain management in care home residents with dementia.

**Methods/design:**

In this two-group, single-blinded, cluster-randomized controlled trial, 122 care home residents with dementia and pain-related diagnoses will be recruited from eight care homes (that is 15 to 16 residents from each care home). Invitations will be sent to all local care homes who meet the home selection criteria. The eight care homes will be randomly selected from all care homes that agree to join this trial. They will then be randomized to either the control or experimental conditions. Participants from each care home will be placed into their home’s corresponding group to avoid ‘contamination’ effects across participants. Each intervention cycle will take 16 weeks (that is, baseline assessment and care home staff training for 4 weeks and Protocol implementation for 12 weeks). The Protocol will guide the pain management of the participants in the experimental care homes. Meanwhile, the control care homes will continue their usual pain management strategies. Intervention effects will be measured weekly during the protocol implementation period and compared with the baseline measurements, as well as between the experimental and control conditions.

**Discussion:**

Although similar pain protocols have been suggested previously, the recommendations were based on experts’ opinions rather than evaluation of research studies. The feasibility and effectiveness of this kind of pain management protocol, tailored to older people with dementia, remains unknown. The findings of this trial will offer strong evidence that better strategies for pain management should be used in the care home daily routine.

**Trial registration:**

The Chinese University of Hong Kong, Centre for Clinical Trials: CUHK-CCT00367

## Background

Despite a high prevalence of pain among older care home residents, pain management for this group remains suboptimal, especially for those with dementia. Among long-term care home residents with dementia, pain often goes unrecognized and under-treated. Evidence shows that these people receive considerably lower doses of analgesics than their cognitively intact counterparts [1]. The discrepancy between the prescribed and actual doses widens as cognition decreases [2]. Residents with dementia are prescribed and administered significantly fewer pain medications and in smaller doses than those without dementia [3,4]. Evidence shows that the provision of inadequate pain treatment for residents with dementia is partly due to inadequate pain assessment and documentation [5].

Lack of a standardized pain assessment tool and proper documentation are major barriers to successful pain management for residents with dementia [5]. Poor pain management in this population has been partly attributed to difficulties with efficient pain assessment. As the deterioration of cognition affects individuals’ ability to report pain, there is an increasing risk that pain will go undetected, leading to poor pain management. Unrelieved pain in residents with dementia may lead to fear of movement, resistance to care, anxiety, and agitated behavior [6]. Untreated pain not only affects their quality of life, but also causes more stress to caregivers dealing with problematic behavior.

During the last decade, much effort has been made to improve pain management for older people who cannot verbalize their pain. Pain experts have suggested strategies for better pain management for them by using observational pain tools, setting standardized pain management strategies, and through education and training [7,8]. Additionally, at least 15 observational pain tools have been developed and validated during the last decade. Generally, preliminary data support the psychometric properties of several observational pain tools [9-12]. The systematic use of an observational pain scale has been advocated as a means to improve pain management [7,8], but so far only one experimental study has been conducted to evaluate the effect of an observational pain tool on pain management. Fuchs-Lacelle et al.’s study demonstrated that regular use of an observational pain scale for 3 months in long-term care homes improved pain management, as evidenced by increased use of analgesics when compared with the control group [13]. However, this study only evaluated a single observational pain tool’s effect in improving pain management practice.

Scale application and score interpretation were considered major challenges to the adoption of an observational pain tool in daily clinical routines. Additionally, none of the behavioral indicators (such as grimacing, fidgeting, crying, shouting, and so on) used in the observational pain tools are unique to pain. There was a concern that misinterpretation of residents’ behavior may lead to inappropriate treatment [14]. Several researchers suggested that observational pain scores should not be considered definitive. Rather, any observational pain tool should be used as part of a comprehensive pain management protocol. All strategies suggested for improving pain assessment and management for people with dementia should be incorporated in the protocol [15-17]. For instance, multiple levels of assessment and treatment should be included in the protocol. In addition to observing residents’ pain-related behavior using an observational pain tool, investigating possible causes of pain, getting information from surrogates, and attempting to obtain self-reported pain should be undertaken for preliminary verification that the observed behavior is pain-related. Observational pain score interpretation should be suggested and pain treatments should be recommended according to the pain scores. Additionally, the protocol should suggest subsequent actions if the behavior persists. This protocol should be used daily. All assessments and treatments should be documented to allow continuous monitoring. However, these suggestions appeared mainly as expert consensus statements [7] or recommendations [15], rather than empirical evidence obtained based on scientific research studies.

In view of this, a comprehensive Observational Pain Management Protocol (Protocol) has been developed and pilot-tested by the first author (JL) in a long-term care home [18]. The flow of this protocol is guided by the pain management process and the corresponding actions (Table 1). The process includes observing and documenting participants’ pain-related behavior using a standard observational pain assessment tool (the Chinese - Pain Assessment IN Advanced Dementia [C-PAINAD]). Other steps include investigating possible causes of pain, getting information from surrogates, attempting to obtain self-reported pain, initiating different types of pain treatment according to observed pain scores, and performing re-assessment after pain treatment.

**Table 1 T1:** Observational pain management protocol

**Process**		**Actions**
1	Pain assessment	Using C-PAINAD for pain assessment
*2a	Score verification	Investigating possible causes of pain (such as injury or pain-related diagnosis), obtaining self-reports if at all possible by asking simple yes/no pain questions to participants, getting information from surrogates, direct contact nurses, and so on
3	Score interpretation	0-1 = no pain; 2-3 = mild pain; ≥ 4 = moderate pain or above
4	Pain-relieving interventions	**Stage one (Pain score > 1)**:
		Initiating pain-minimizing and caregiving guidelines^a^
		**Stage two (Pain score > 4)**:
		Non-pharmacological treatments: hot therapy, cold therapy, TENS, massage, and so on
		- Consulting in-house physiotherapists, occupational therapists and nurses about the selection of treatment(s)
		- Pharmacological treatments: analgesic trial
		- Administering regular/‘if needed’ (PRN) analgesic medications 30 minutes before pain-triggered nursing procedures
		- When no analgesic has been prescribed, discussing with resident’s physician whether or not to prescribe analgesics
5	Evaluation and continued monitoring	Monitoring the effectiveness of the implemented interventions by C-PAINAD
		- Decreased pain score - continued monitoring
		- If pain-related behavior persists - modify interventions
6	Documentation	All pain scores and pain treatments administered to participants must be recorded on the pain chart
2b	*Verification - no evidence indicates pain	- Attempting to interpret meaning of behavior with help of caregivers who are familiar with the residents
		- Ensuring basic needs are met

^a^Please refer to Table 2 for detailed descriptions of the Pain-minimizing and Caregiving Guidelines.

The Protocol was used to guide the pain management of 30 care home residents with dementia, with at least one pain-related diagnosis, for 8 weeks. Before the implementation, only five residents had been prescribed pain medications. Pain medications administered to the residents were quantified by the Medication Quantification Scale (MQS) [19]. During the study period, the mean MQS score increased from 10 (SD 14.23) at week 1 to 23.41 (SD 10.58) at week 8. The percentage of residents given pain medications increased to 23.33% (n = 7) at week 8. Similarly, only six residents were receiving non-pharmacological interventions at week 1. Towards the end of the study period, 17 residents were receiving non-pharmacological pain-relieving interventions such as hot pads, ice therapy, and massage. The mean pain score of the 30 residents decreased slightly from 2.87 (SD 1.30) at week 1 to 2.57 (SD 1.32) at week 8. Although this study did not show a statistically significant reduction of pain scores, probably due to the small sample size, it did show clinical relevance in improving pain management. Incorporation of this Protocol into the long-term care home’s daily routine encouraged well-organized pain recording for each resident, allowing further comparisons of pain treatment effectiveness. Besides this pilot study, no other study has been conducted to evaluate the effectiveness of similar protocols in improving pain management practice.

The aim of this study is to investigate the extent to which the implementation of the Observational Pain Management Protocol can improve the management of pain for older care home residents with dementia. Based on the findings in our pilot study [18], we hypothesize that the implementation of the Protocol will result in an improvement in pain management for residents with dementia, as manifested in an increased use of both pharmacological and non-pharmacological pain treatments. As a consequence, behavioral pain scores will be lower due to better pain management. The following two research objectives have been derived:

1. To investigate whether a systematic use of the Protocol improves pain management, as manifested by the increased use of pharmacological and non-pharmacological pain treatments for residents with dementia.

2. To investigate whether the use of this Protocol results in lower observational pain scores for residents with dementia.

## Methods/design

### Study design

A two-group, single-blinded, cluster-randomized controlled trial (RCT) will be used to examine the effect of the Protocol on pain management for older people with dementia as compared to a control condition of usual pain management practice in long-term care homes. This study will take 16 weeks (that is, baseline assessment and care home staff training for 4 weeks and Protocol implementation for 12 weeks). Participants in the control condition will continue usual pain management practice according to their care homes. Intervention effects will be measured weekly and compared with the weekly baseline measurements for 4 weeks, as well as between the experimental and control conditions, to detect the progress of the effectiveness of the Protocol in pain management continually throughout the study period. The overall study design is illustrated in Figure 1.

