#### *Baseline assessment*

Baseline assessment will include the weekly MQS III score and the weekly record of non-pharmacological pain treatments. Participants’ daily use of pain medications will be quantified into the MQS III scores. Other non-pharmacological pain-relieving interventions will also be recorded daily. Both of these records will be collected weekly for the first 4 weeks of the intervention cycle by the designated research assistant (RA). This collection will continue for the 12 weeks of the Protocol implementation in the experimental care homes or during the usual pain management period in the control care homes. In addition, participants’ C-PAINAD scores will be collected by the independent pain observer once a week throughout the 16-week study period. Please refer to the section below for a detailed explanation of the role of the independent pain observer.

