#### *Implementation of the Protocol in experimental long-term care homes*

Four 1-hour workshops will be conducted by JL during the first 4 weeks of the intervention cycle. These will aim to ensure that both professional and non-professional care home staff understand and follow the Protocol correctly. Workshop I will introduce pain assessment and management for older people with dementia. Workshops II and III will explain the use of the Protocol for their pain assessment and treatment. The staff will practise pain assessment by C-PAINAD through various pre-developed clinical vignettes. They will also learn to discriminate between various steps of pain treatments based on the pain score. Group discussions will be held after the practice. The staff will be asked to explain their choice of indicators and give reasons for their choice. They will also be asked to explain their subsequent actions in terms of the selection of different stages of pain treatments suggested by the Protocol. Through practice and discussion sessions, the staff should be able to follow the Protocol. Workshop IV is mainly about the implementation of the Protocol. Finally, a test will be conducted to ensure that the staff understand the Protocol. Given that the job nature and educational backgrounds of professional and non-professional caregivers are different, they will attend the workshops separately. The workshops’ contents will be tailored to suit these two groups of staff.

Following the training workshops and after ensuring that all care home staff understand and can follow the Protocol (Table 1), it will be formally incorporated into the care homes’ daily routine.

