#### *Control long-term care homes*

As in the experimental long-term care homes, four 1-hour workshops will be conducted by JL, addressing pain assessment and management for older people, during the first 4 weeks of the intervention cycle. The control care homes will continue their usual pain management strategies for the participants for the remaining 12 weeks of the intervention cycle. Similarly, participants’ weekly C-PAINAD scores will be collected by the independent pain observer throughout the 16-week study period. Their weekly MQS III score and weekly record of non-pharmacological pain treatments will be collected by another RA throughout the intervention cycle.

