### Blinding

Two RAs, who will be blinded to the study hypothesis and group allocation, will be responsible for all subject assessment measures. One will be responsible for collecting MQS III scores and non-pharmacological pain treatment records. Another will work as the independent pain observer to collect participants’ observational pain scores. The pain observer will also be blinded to participants’ total pain medication consumption. We anticipate that after the training sessions, the staff in the care home will become more sensitive to residents’ behavioral patterns. To avoid a contamination effect caused by different time points in the Protocol implementation of different participants within the same care home, the pain management Protocol will be implemented for all participants in each care home simultaneously.

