### Outcome measures

The effectiveness of the Protocol on pain management will be evaluated by: (1) the use of pharmacological pain treatments, measured by the Medication Quantification Scale III (MQS III); (2) the use of all non-pharmacological pain treatments recorded on the participants’ pain management record; and (3) pain-related behaviors exhibited by participants, which will be assessed by an observational pain scale (that is, C-PAINAD). The Protocol will be used to guide the pain management of the participants in the experimental condition for 12 weeks (that is, from the fifth to the sixteenth weeks of the intervention cycle). Intervention effects will be measured weekly and compared with the baseline measurements as well as between the experimental and control conditions to detect the progress of the effectiveness of the Protocol in pain management continually throughout the study period. Baseline measurements will be collected for 4 weeks (that is, between the first and fourth weeks of the intervention cycle).

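### Weeks 1 to 4 are both baseline and staff training, so the baseline can carry some training effect; separately, control homes also get pain workshops, so the comparator is more than usual practice

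*Protocol article*

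**What the plan says.** **Timetable.** Study design divides the study as follows: "baseline assessment and care home staff training for 4 weeks and Protocol implementation for 12 weeks".

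**Baseline.** Outcome measures places the baseline "between the first and fourth weeks of the intervention cycle". For MQS III and non-pharmacological treatment, Baseline assessment adds: "Both of these records will be collected weekly for the first 4 weeks of the intervention cycle". C-PAINAD is scored weekly over all 16 weeks by an independent observer. Statistical analysis and outcome measurement plans a before-after test in the experimental group, between-group tests of the outcome variables, and mixed-effect modelling of change relative to baseline.

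**Training, experimental homes.** The section on implementation in experimental homes schedules four 1-hour workshops "during the first 4 weeks of the intervention cycle. These will aim to ensure that both professional and non-professional care home staff understand" how the Protocol works. On content it says: "Workshops II and III will explain the use of the Protocol for their pain assessment and treatment". Formal use of the Protocol follows the workshops, from week 5.

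**Expected effect of training.** The Blinding section anticipates that "after the training sessions, the staff in the care home will become more sensitive to" how residents behave.

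**Control homes.** Study design describes the trial "as compared to a control condition of usual pain management practice in long-term care homes", and the Abstract likewise has control homes continuing their usual strategies. Control long-term care homes, however, gives these homes four 1-hour workshops too, "addressing pain assessment and management for older people, during the first 4 weeks of the intervention cycle". Their usual strategies then continue for the remaining 12 weeks.

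**The concern.** Two separate matters arise from the same four weeks.

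The first is the reference point for change. MQS III and the non-pharmacological record measure what staff give or initiate. If staff begin to act differently as they are trained, these outcomes can move before week 5, and an analysis that subtracts the week 1 to 4 values subtracts some of what it is meant to detect. No section says that any baseline reading precedes Workshop I.

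The second is the name of the comparator. Homes whose staff have had four hours of teaching on pain assessment and management are not simply homes under usual practice. A reader of the Abstract or Study design would attach the result to a comparison that the trial does not make.

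**Working it through.** The plan gives no figure for a training effect, so there is none to reproduce. The check is algebraic, followed by a range under stated assumptions.

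**Notation.** Let μ be the level under untrained usual practice, the same in both arms. Let E be the shift in experimental homes during follow-up and c the shift that the workshops produce in control homes during follow-up. Let t_E and t_C be the shifts that training has already produced in the baseline value of each arm.

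| Quantity | Experimental | Control |
|---|---|---|
| Baseline | μ + t_E | μ + t_C |
| Follow-up | μ + E | μ + c |

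**What each planned analysis estimates.**

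1. Pre-post in the experimental arm: (μ + E) − (μ + t_E) = E − t_E. The whole of t_E is lost.
2. Between-arm difference at follow-up only: (μ + E) − (μ + c) = E − c. Neither t_E nor t_C appears.
3. Between-arm difference in change from baseline: (E − t_E) − (c − t_C) = (E − c) − (t_E − t_C). Only the difference between the arms' training effects matters. It is zero if the two are equal. It pulls towards no effect if t_E exceeds t_C in the direction of benefit, and the other way if t_C is larger.

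**Could t_E and t_C differ?** Yes. Only the experimental workshops are described as teaching the Protocol; the control workshops cover pain assessment and management for older people. The documents do not say by how much the effects would differ.

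**Illustrative size.** Let f be the share absorbed: t_E/E for analysis 1, (t_E − t_C)/(E − c) for analysis 3. With the variance unchanged, required n is proportional to 1/(effect)², so it grows by 1/(1−f)².

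- f = 0%: 1/1.00² = 1.0
- f = 10%: 1/0.90² = 1/0.81 = 1.23
- f = 25%: 1/0.75² = 1/0.5625 = 1.78

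One route to 25% in analysis 1: training effects of 0, 1/6, 1/3 and 1/2 of the full effect in weeks 1 to 4, averaged over the four weeks, give (0 + 1/6 + 1/3 + 1/2)/4 = 1/4. Both the rise and the averaging are assumptions; the protocol speaks of weekly baseline measurements and does not say that they are averaged. For analysis 3, a baseline shift of 25% of (E − c) in experimental homes and 15% in control homes leaves f = 25% − 15% = 10%.

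**Comparator.** A contrast with untrained usual practice would be E. The trial estimates E − c at follow-up. That is a valid randomised quantity under a different description, and the two coincide only if the control workshops have no effect (c = 0).

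**The case against.** The strongest defence is that the intervention is the Protocol, which enters daily routine only after the workshops and a test of staff understanding. Weeks 1 to 4 then hold at most a partial effect of training. Workshop I is introductory, and the workshops are not dated within the four weeks, so some baseline readings may be clean. The Blinding statement concerns the time after the sessions and is offered as the reason for starting all participants in a home together; it does not say that treatment rises during baseline. Where no analgesic is prescribed, new use depends on discussion with a physician, so a lag is plausible. C-PAINAD outcome scores come from a blinded observer during a standardised exercise, not from newly trained staff. All of this stands. It limits the claim to what the baseline can contain and leaves the size unknown.

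On the comparator, the control workshops are openly described, and equal workshop contact helps to separate the Protocol from staff attention and education. That is a reasonable design. It does not reconcile the Study design and Abstract wording with the control-home section.

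A reader might go further and infer that the baseline already holds intervention effect, that every baseline-referenced result is biased towards no effect, or that training control homes undermines the randomised comparison. The documents support none of these. A training shift common to both arms cancels in the between-arm change, the direction of any residual depends on which arm shifts more, and control training alters what is estimated without biasing the randomised contrast.

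**Conclusion.** The point holds in limited form. It is certain from the text that baseline and training share weeks 1 to 4 and that control homes are trained. It follows that the experimental-arm pre-post test can be attenuated, and that the between-arm change from baseline is affected only if training effects differ between arms. Between-group comparisons of follow-up values are not biased by the overlap.

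The size is unknown. The factors 1.0 to 1.78 rest on assumed absorbed shares of 0% to 25% and an unchanged variance; they are not estimates for this trial.

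The comparator label is incomplete as it stands, whatever the size of any training effect. The design supports a conclusion about the Protocol's effect beyond pain education, not about its effect against untrained usual practice.

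**What to change.** 1. **Take the reference baseline before Workshop I.** For MQS III and non-pharmacological treatment, look back through existing records for the weeks before the first workshop. Participants must have lived in the home for more than 6 months, and non-pharmacological data already come from nursing and therapy records, so such records should exist. For C-PAINAD, schedule the week-1 observation before Workshop I. Report the later baseline weeks as a training phase, and keep the four-week C-PAINAD baseline as a sensitivity analysis.
2. **Describe the comparator throughout as usual practice plus pain-education workshops**, including in the Abstract and Study design, and limit the conclusion to the Protocol's effect beyond that education.

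**Cost.** The C-PAINAD baseline rests on one reading instead of four and is noisier; the documents give no within-person variance from which to say by how much. Workshop I must follow the week-1 observation in every home, which is a small scheduling constraint. The look-back adds some data collection, and it should be checked that earlier records show treatment times as fully as prospective ones. The claim becomes narrower. Trial status says that care homes are still being recruited, so both changes are feasible.
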